## Abstract

Empathy is positively related to healthcare workers and patients’ wellbeing. There is, however, limited research on the effects of empathy education delivered in acute clinical settings and its impact on healthcare consumers. This research tests the feasibility and the potential efficacy outcomes of an immersive education programme developed by the research team in collaboration with clinical partners and a multidisciplinary advisory group. Healthcare worker participants in the intervention ward will receive an 8-week immersive empathy education. The primary outcome (feasibility) will be assessed by evaluating the acceptability of the intervention and the estimated resources. The secondary outcome (efficacy) will be assessed using a quasi-experimental study design. Non-parametric tests will be used to test healthcare worker participants’ empathy, burnout, and organisational satisfaction (within-group and across groups), and healthcare consumer participants’ satisfaction (between-group) over time. Despite growing interest in the importance of empathy in professional relationships, to our knowledge, the present pilot study is the first to explore the feasibility and efficacy of an immersive empathy education in New Zealand. Our findings will provide critical evidence to support the development of a randomised cluster trial and potentially provide preliminary evidence for the effectiveness of this type of empathy education.

## 1. Introduction

### 1.1. Background and Rationale

Empathy is a fundamental component of therapeutic relationships in healthcare, conferring benefits for both healthcare workers (HWs) and healthcare consumers (HCs). For example, empathy is associated with increased wellbeing among healthcare providers, such as greater mental health [1], lower levels of burnout [2], and higher levels of collaboration [3]. Empathy is also related to patients’ psychological wellbeing and physiological outcomes [4]. For example, HWs’ empathy is associated with patients’ tendency to disclose more information [5,6,7], and to better control their chronic health condition [8]. The systematic review of Derksen et al. [4] found that in the presence of physician empathy, patients experienced decreased anxiety and distress and clinical outcomes were enhanced. This perception of physician empathy has even been found to decrease the severity and duration of the common cold [9]. Compassionate and empathetic care factors in patients’ evaluations of their HW [10,11] as shown in patients’ tendency to make personal recommendations for specific physicians [12]. In summary, empathy in healthcare can help HWs to positively influence HCs’ healthcare outcomes as well as contributing to their own feelings of wellbeing.

Despite the benefits of empathy in the clinical setting, evidence suggests that empathy is often missing across the healthcare system [10,13,14,15]. Multiple studies have found that HWs’ empathy declines over the course of medical training [16,17,18,19]. For example, 61% and 23% of surveyed medical residents reported becoming more cynical and less humanistic, respectively, over the course of their residency training [20]. Lack of empathy is associated with higher levels of self-perceived medical error [21], resulting in increased risk to patients. Thus, evidence indicates that there is an emerging need to foster empathy in healthcare.

An individual’s capacity for empathy is influenced by personal and environmental characteristics and can be enhanced through education [22]. Meta-analysis indicated that empathy training sessions and programmes are effective tools to enhance empathy, especially among healthcare professionals and university students [23]. For example, empathy training improved physicians’ ability to read emotional expressions, and resulted in higher empathy scores rated by patients [24]. Furthermore, greater effects were found in studies where participants were compensated for their involvement, empathy measures exclusively focused on understanding and reporting emotions, and when using objective rather than self-reported measures [23]. A systematic review specifically examining empathy education in undergraduate nursing students found that studies that used immersive interventions were the most effective [25], suggesting that immersive education programmes are a promising direction for developing successful education. Despite these advancements in the study of empathy, more research is required to determine the magnitude and duration of effects of different types of empathy training programmes [22,26], different population groups, training settings, and types of assessment measures [23].

In New Zealand, studies on healthcare quality and specifically on empathy are limited. Therefore, measuring national healthcare quality, safety and experience of care has become an overarching national goal set by the Health Quality & Safety Commission [27]. As there is no evidence of exploration of empathy education in the context of the wider healthcare team or its impacts on healthcare consumers in New Zealand, the current research aims to address this gap by developing and testing the feasibility and efficacy of delivering an immersive empathy education programme (EmpEd) to a multidisciplinary healthcare team in the clinical setting. Assessing the feasibility and efficacy of a newly developed empathy education programme is pivotal to develop and design a high quality, high potency education package that effectively supports a healthy ward culture and fosters healthcare consumers’ experiences of empathetic care. This protocol outlines the primary and secondary objectives of this research, the development plan and the implementation of the EmpEd, and the assessment plan of its potential efficacy outcomes.

### 1.2. Objectives

The primary objective of this pilot study is to evaluate the feasibility of the developed immersive Empathy Education Programme in the clinical setting. First, feasibility will be determined by assessing HWs’ acceptance of the intervention. Acceptability will be measured by five indicators: recruitment rates; completion rates; drop-out rates, HW participants’ written feedback; and their oral evaluation of the programme. Second, feasibility will be evaluated by estimating the programme costs and organisational resources needed to facilitate an EmpEd in the future including time commitment, material and financial resources required to run the programme. The secondary objective is to assess the efficacy of the proposed EmpEd. This secondary objective is dependent on the outcome of the feasibility assessment. That is, if the delivered EmpEd’s acceptance level enables us to collect data and ensure acceptable power for statistical analysis, then we will assess HWs’ level of empathy, subjective wellbeing, organisational satisfaction, and HCs’ satisfaction over time.

## 2. Method

### 2.1. Design

This quasi-experimental study of healthcare workers and healthcare consumers is a feasibility and pilot study to form the basis for a future, prospective cluster randomised trial (CRT). The single centre study will be conducted at one tertiary hospital in New Zealand. To minimise harm to participants, the key characteristics that will guide the ward selection are stable workforce, predictable patient population, and stable leadership. Based on local conditions, the Chief Nursing Officer will identify and select two wards (intervention and control ward) that meet these criteria. Although everyone on the wards will be invited to participate in the study, it is reasonable to expect that not everyone would want to be enrolled in the research. Thus, the wards are the study setting, and the groups are the enrolled participants on the wards.

Participants will be pre-allocated into four groups. Based on the participants’ location in the hospital, they will be either part of the intervention or the control group. Based on the participants’ position in the healthcare system, they will be either part of the HW group or the HC group. Participants in the HW groups will be constant during the study, while participants in the HC groups will differ across time points. HWs in the intervention ward/group will receive an 8-week immersive empathy education programme and the control ward/group will operate as usual during the research study. HCs will receive care, support and will interact with healthcare workers as usual in both wards/groups. HCs in the intervention ward/group will not be directly affected by the intervention; however, they will experience limited exposure to the education programme (e.g., seeing educational materials on the ward walls).

The study duration is expected to be approximately 30 weeks (see Figure 1 for the outline timetable for participants). The study will begin with a 3-week recruitment and consenting period prior to delivering the intervention. Baseline assessment of all participants will be continuous in this 3-week period (Weeks 1–3). This is followed by the 8-week intervention. The research team will deliver the immersion programme in the intervention ward, while the control ward will continue to operate as usual with no interaction/engagement during this time with the research team (Weeks 4–12). After delivering the intervention, all participants will complete the second assessment (Week 13–15). HWs in the intervention ward will be invited to participate in focus group interviews about their experiences of the EmpEd (initiation, Week 13; interviews, Weeks 16–17). Three months later, a final follow-up assessment of all participants will complete the quasi-experiment (Weeks 27–30). The design is adaptive in that the study duration and the intervention can be changed if participation and feedback from study participants indicate necessary adjustments for successful study continuation.

An advisory group will be established, and will be made up of health care professionals, healthcare consumer representatives, cultural advisors, and international experts in empathy education. The purpose of the advisory group is to ensure that relevant perspectives and voices are heard and considered in the design of the intervention and the assessment of the EmpEd (e.g., considering different value orientations in a multicultural environment, the work schedule of HW participants, and access to resources). Three advisory meetings will be held over the course of the programme, and a 100 NZD gift voucher per meeting will be offered to each advisor for their contribution.

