### 3.3. Sample Size Calculation

Two independent HW groups will be assessed across three time points. An estimated 55 staff in each group (110 total) is required to achieve at least 80% power to detect a difference in the outcome measures as a response to the intervention. Applying the Bonferroni correction, the significance level for each test is adjusted to α = 0.05/9 = 0.0056. To assess HCs, initial power calculations suggested that for each HC group, a sample size of 50 per group per timepoint in each ward (300 participants) would result in a confidence interval limit of ±0.139 or 13.9% on a result of 0.5 or 50%. However, we expect that it would be difficult to achieve a sample size of >25 per group. The validity assessment will guide decisions regarding whether combining the two HC groups (patients and support persons) into one HC group per ward per timepoint is advisable. This part of the study is subject to modification and treated as exploratory. Power calculations were conducted in G*Power Version 3.1.9.4 for Windows.

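### With one selected ward per arm, 55 staff per ward cannot give 80% power for an intervention effect; at most they give power for a difference between these two sets of staff

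*Protocol article*

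**What the plan says.** Section 2.1 (Design) sets up two wards at one hospital: "the Chief Nursing Officer will identify and select two wards (intervention and control ward) that meet these criteria". Individuals follow their ward: "Based on the participants’ location in the hospital, they will be either part of the intervention or the control group". The section treats the ward as background only: "Thus, the wards are the study setting, and the groups are the enrolled participants on the wards".

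Section 3.3 (Sample Size Calculation) describes the two staff groups as independent and says that an estimated 55 per group, 110 in all, "is required to achieve at least 80% power to detect a difference in the outcome measures as a response to the intervention". It sets a Bonferroni level of 0.05/9 = 0.0056 per test. It calls the healthcare consumer part exploratory but does not say this of the staff part. Section 3.4 plans nonparametric tests across time points and between groups.

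Section 1.2 (Objectives) makes the efficacy assessment depend on whether acceptance of the programme "enables us to collect data and ensure acceptable power for statistical analysis".

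The article does not say anywhere that a ward effect and a programme effect cannot be told apart in this design.

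**The concern.** The programme acts on a ward as well as on individuals: section 2.4 describes ward branding, a staff quiet space, a refreshment trolley and group mindfulness sessions. With one ward per arm, any difference may come from the programme or from anything else that differs between the wards. Recruiting more staff on the same two wards does not help; only more wards per arm would.

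Section 3.3 nevertheless attaches a power figure and an adjusted significance level to a response to the intervention. A reader of the results could then take a significant test as adequately powered evidence of efficacy, when it shows only that two wards differed or changed differently. The Discussion looks ahead to a cluster randomised trial and, if the programme succeeds, to use across all District Health Boards, so the distinction has consequences. The power condition in section 1.2 also rests on a quantity that the design cannot supply for an intervention effect.

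**Working it through.** **Inputs from the article.** Two wards and two arms (2.1); 55 completing staff per ward (2.2, 3.3); level 0.05/9 per test and power of at least 80% (3.3); the same staff assessed at baseline and twice later (2.1).

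**Assumptions, not in the article.** Two-sided tests; ICC for ward 0.01 to 0.05; for change scores, within-person correlation ρ = 0.5 and cluster autocorrelation c = 0.5 to 0.8.

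**1. The plan's own figures.** 0.05/9 = 0.00556, which rounds to the stated 0.0056. The 55 per group cannot be reproduced, because the article gives no effect size and names no test. The full protocol may do so, and this is not counted as an error. Solving for the detectable difference with independent individuals:

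(2.773 + 0.842) × √(2/55) = 3.615 × 0.1907 = 0.69 SD

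The t test gives 0.70 and the Wilcoxon test (efficiency 0.955) gives 0.72. So 80% power is attainable for a difference of about 0.7 SD, provided that the ICC is zero.

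**2. Information about the intervention.** Between-ward degrees of freedom = 2 wards − 2 arms = 0. This needs no assumed ICC and does not depend on the number of staff. The data contain no estimate of ward-to-ward variation against which a programme effect could be tested.

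**3. Illustration for one cross-sectional comparison.** The true variance of the difference in ward means, divided by the variance that an individual-level test uses, is (1 + 54 × ICC)/(1 − ICC). With no programme effect, the true rejection rate is 2 × [1 − Φ(z/√ratio)], with z = 2.773 (nominal 0.0056) or 1.960 (nominal 0.05).

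| Assumed ICC | Ratio | True rate at nominal 0.0056 | True rate at nominal 0.05 |
|---|---|---|---|
| 0.01 | 1.54/0.99 = 1.56 | 2.6% | 11.6% |
| 0.02 | 2.08/0.98 = 2.12 | 5.7% | 17.9% |
| 0.05 | 3.70/0.95 = 3.89 | 16.0% | 32.1% |

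Using the plain design effect (1.54, 2.08, 3.70) instead gives 2.6%, 5.4% and 14.9% at nominal 0.0056. Simulated Mann-Whitney tests (20,000 per setting) gave 0.5% at ICC 0, 5.1% at 0.02 and 14.5% at 0.05. For a rank test the upper end is thus nearer 15% than 16%.

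**4. Illustration for change from baseline.** Stable ward differences cancel. The ratio becomes 1 + 55 × ICC × (1 − c)/[(1 − ICC)(1 − ρ)].

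- ICC 0.01, c = 0.8: 1 + 0.11/0.495 = 1.22, true rate 1.2% at nominal 0.0056.
- ICC 0.05, c = 0.5: 1 + 1.375/0.475 = 3.89, true rate 16%.

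If c were 1, meaning no ward-by-time variation, the ratio would be 1 and there would be no inflation.

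**5. What 55 per ward does give.** The 95% half-width for the two-ward difference in mean change is about 1.96 × √(2/55) = 0.37 SD of the change score. It covers variation between staff only, not between wards.

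**The case against.** The strongest reply is that this is a declared quasi-experimental feasibility pilot. Acceptability and resources are primary, efficacy is secondary and conditional, and the Abstract says only that the findings may "potentially provide preliminary evidence for the effectiveness of this type of empathy education". Two wards before a cluster trial is a disclosed choice. Both wards must also have steady staffing and leadership and a foreseeable patient mix (2.1, repeated in 2.2), and staff who work on both are excluded. All of this stands and limits the severity. It does not rescue the power sentence. The selection criteria narrow the differences between the wards without separating ward from programme, and only the consumer part is labelled exploratory.

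A second reply is that the same staff are measured three times, so stable ward differences drop out of a comparison of changes. This also stands. What remains is ward-by-time variation. The Discussion itself expects staff reallocation, heavy workload and COVID-19 disruption, any of which can fall unequally on two wards. Within-group tests do not help, since they cannot separate the programme from the passage of time.

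Four stronger readings are tempting but not supported:

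- *That 16% is this study's error rate.* It is one end of an illustration under an assumed ICC; the article gives none.
- *That a more receptive ward will be picked.* Selection is not random, but nothing in the text suggests this.
- *That section 1.2 plans selective reporting.* The condition there mainly concerns having enough data, and section 3.4 commits to manuscripts covering both feasibility and efficacy. The Discussion words the dependence more loosely, so clarification is reasonable.
- *That drawing lots for the ward after baseline would cure the problem.* It would still leave one ward per arm. It would also conflict with pre-allocation (2.1) and with prize draws that differ by arm from the baseline period on (2.3).

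**Conclusion.** The point holds. The claim in section 3.3 of at least 80% power for a response to the intervention describes a property that the design does not have. This conclusion rests only on one ward per arm and allocation by location, both stated in section 2.1, and on no assumed parameter. At most, 55 per ward gives 80% power for a difference between these two sets of staff of about 0.7 SD, if ward-level variation is zero.

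Individual-level p-values overstate the evidence by an amount that cannot be fixed from the article. The illustrations run from about 2.6% to 16% true error at nominal 0.0056 for one cross-sectional comparison, and from 1.2% to 16% for changes from baseline, under the assumptions listed above.

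Severity is moderate. Feasibility is primary and unaffected, and two wards can serve a pilot. A reader might infer that the efficacy data are worthless or that the study should not proceed. The document supports neither; what needs correcting is what the staff comparison is said to show.

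**What to change.** 1. **Section 3.3.** Replace the power claim with a precision statement, for example: with 55 completing staff per ward, the 95% confidence interval for the difference between the two wards in mean change from baseline extends about 0.37 SD of the change score either side, reflecting variation between staff only; the design supports no power statement for an intervention effect.
2. **Section 3.3.** Label the staff efficacy outcomes exploratory, as is already done for the healthcare consumer outcomes.
3. **Section 3.4.** Report estimates with 95% confidence intervals as two-ward differences in change, and make no claim of efficacy based on significance.
4. **Sections 2.1 and 4.** State as a limitation that ward and programme effects cannot be separated, and that baseline data remove only the stable part of the ward difference.
5. **Section 1.2.** Replace the condition on acceptable power with a commitment to report whatever efficacy data are collected.

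The cost is wording only: no extra wards or staff and no change to the timetable. The downside is weaker language about efficacy.

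### Ward roles are fixed before healthcare workers consent and complete baseline, so the two enrolled groups may self-select differently and baseline answers may be coloured by arm

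*Protocol article*

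**What the plan says.** Section 2.1 (Design) of the protocol article fixes the ward roles at the outset: "the Chief Nursing Officer will identify and select two wards (intervention and control ward) that meet these criteria". Individual arm then follows from workplace: "Participants will be pre-allocated into four groups. Based on the participants’ location in the hospital, they will be either part of the intervention or the" (the sentence goes on to name the other arm). Enrolment is voluntary and expected to be partial: "it is reasonable to expect that not everyone would want to be enrolled in the research". The comparison is between volunteers, not whole wards: "the groups are the enrolled participants on the wards".

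The same section places recruitment, consent and baseline together before the programme: "Baseline assessment of all participants will be continuous in this 3-week period (Weeks 1–3"). Delivery starts in Week 4. Section 2.3 (Procedure) describes recruitment by presentations, posters and one-to-one conversations, and excludes anyone who discontinues from all analyses.

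Section 1.2 (Objectives) makes recruitment part of the primary objective: "Acceptability will be measured by five indicators: recruitment rates; completion rates; drop-out rates", followed by written and oral feedback. Section 2.1 states that the pilot is meant to underpin a later cluster randomised trial.

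**The concern.** Staff on the two wards are deciding about different things. On one ward, joining means an 8-week empathy programme plus surveys. On the other, it means surveys while work goes on as usual. People drawn to an empathy programme may differ in empathy, burnout or motivation from people willing to fill in three surveys. This acts on individuals and would arise even with many wards per arm, so it is separate from having one ward per arm.

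Baseline does not sit safely before the problem. The empathy, organisational satisfaction and professional quality-of-life scales are all self-reported and are completed after the ward roles are set. If answers depend on the arm expected, the reference point for later change is itself affected.

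At stake are the between-ward healthcare worker contrasts and the reading of recruitment rate, which is one of the primary feasibility indicators. The problem is largely avoidable, because nothing in the timetable needs the roles to be known before Week 4.

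**Working it through.** **1. Order of events.** Roles designated (Section 2.1) → staff approached (Section 2.3) → consent and baseline, Weeks 1–3 (Section 2.1) → programme from Week 4. No step withholds the ward role.

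**2. Is the arm known at consent?** No sentence says so, and the information sheet is not shown. Three features point that way:
- "Participants will be pre-allocated into four groups" places group membership before enrolment (Section 2.1).
- Prize draws differ by arm: three for control staff, one for intervention staff (Section 2.3).
- Staff are surveyed on their prior expectations of the intervention (Section 3.1).

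The exclusion of staff who work on both wards (Section 2.2) needs only the identity of the two wards, not their roles.

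**3. The plan's own figures.** Section 3.3 gives α = 0.05/9 = 0.0056, which reproduces. The 55 per ward cannot be reproduced, because no effect size, SD or test is stated. Inverting the two-means normal approximation gives (2.773 + 0.842) × √(2/55) = 0.69 SD as the difference detectable with 80% power, two-sided.

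**4. Possible trait shift (assumed inputs).** If a fraction p of each ward joins and willingness correlates ρ with the trait, volunteers exceed their ward mean by ρ × φ(z)/p SD, where z is the cut-off leaving a fraction p above it. The factor φ(z)/p is 0.798 at p = 0.5 and 0.497 at p = 0.7. With equal uptake, only the difference in ρ between wards counts:

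| Difference in ρ | Shift at p = 0.7 | Shift at p = 0.5 |
|---|---|---|
| 0.1 | 0.05 SD | 0.08 SD |
| 0.2 | 0.10 SD | 0.16 SD |
| 0.4 | 0.20 SD | 0.32 SD |

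The documents give neither uptake nor any correlation.

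**5. Effect on an unadjusted comparison.** With no programme effect and a shift of b SD, the two-sided rejection probability is 1 − Φ(z_α/2 − b/√(2/55)) + Φ(−z_α/2 − b/√(2/55)), with √(2/55) = 0.191:

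| b | nominal 0.0056 | nominal 0.05 |
|---|---|---|
| 0 | 0.56% | 5.0% |
| 0.1 SD | 1.3% | 8.2% |
| 0.2 SD | 4.2% | 18.2% |
| 0.3 SD | 11.5% | 35.0% |

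These hold for a follow-up comparison that ignores baseline. The protocol specifies only nonparametric analyses across time points and between groups, so the table is an illustration, not a prediction.

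**6. Comparing changes instead.** Let the intervention volunteers carry a constant trait shift b, an arm-related reporting shift r₀ at baseline and r₁ at follow-up, and an extra change g that they would have shown anyway. The difference in change is then (b + r₁ + g) − (b + r₀) = g + (r₁ − r₀). The constant b cancels. Differential change does not, and neither does arm-coloured reporting unless it is equal at both times. The documents allow no estimate of g, r₀ or r₁.

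**7. Recruitment rate.** Each ward's rate measures uptake of its own offer. As an assumed example with wards of equal size, 80% and 50% pool to (80 + 50)/2 = 65%, which describes neither offer.

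**The case against.** The design is openly called quasi-experimental, the sample is a convenience sample, and efficacy is secondary and conditional on feasibility. With one ward per arm, ward and programme effects stay inseparable however staff are recruited. All of this stands, and it limits how much the efficacy contrast can gain. It does not cover self-selection of individuals after allocation, which the protocol does not discuss.

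Second, Section 1.2 uses recruitment rate as a sign that staff accept the intervention, and uptake of a known programme offer measures that directly. This also stands. Concealing the roles changes what the rate means, so the fix must say where acceptance is then read.

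Third, concealment up to baseline does not blind follow-up. Control staff may also withdraw once they learn their ward will not receive the programme, and under Section 2.3 they would then be removed from every analysis. This too is right, and the fix has to address it.

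Three stronger readings are tempting but not supported:
- A reader might infer that every assignment is known before consent. That is a strong inference, not something stated.
- A reader might infer that recruitment rates cannot carry over to the cluster trial. That depends on whether the trial recruits staff before or after randomisation, which is not given. If after, ward-specific rates could be informative.
- A reader might take the error rates in the working as the plan's own. They need an assumed shift and an unadjusted comparison that the plan does not specify.

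**Conclusion.** The point holds as an avoidable design weakness, not an internal contradiction. Ward roles precede consent and baseline, no concealment is described, and the two offers and incentives differ. The enrolled groups may therefore select themselves differently, and baseline may be coloured by arm, in addition to the declared ward-level confounding.

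The size is unknown. Differences of 0.1–0.4 in the selection correlation, with 50–70% uptake in both wards, give 0.05–0.32 SD. That matters for a comparison that ignores baseline and cancels in a comparison of changes if it is constant. The part that baseline cannot remove, arm-coloured reporting and differential change, cannot be quantified from the documents.

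Recruitment rates under two offers may not carry over to a cluster trial that recruits before randomisation. The conclusion rests on the inference that staff know their ward's role at entry, which the text makes very probable but does not state.

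**What to change.** In Section 2.1:

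1. The Chief Nursing Officer selects two eligible wards that could each host the programme, without naming roles. Replace the pre-allocation wording accordingly.
2. Both wards are recruited with one common information sheet and presentation, stating that one of the two will receive the programme from Week 4.
3. Healthcare worker consent and baseline close at the end of Week 3. Only then is the intervention ward announced, preferably after one recorded draw by someone outside the research team and the wards.

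In Sections 2.3 and 3.1:

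4. Report recruitment by ward, not pooled.
5. Report withdrawal after the announcement by ward. Keep those who withdraw after baseline in the feasibility denominators and in every analysis for which they have data, and amend the exclusion of discontinuers to match.
6. Word the expectations question conditionally, or ask it after the announcement.

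The cost is protocol wording, one shared information sheet and one draw, with no added participants or visits and no change to the 30-week timetable. There are three downsides. Both wards must provisionally be able to host the programme (quiet space, mindfulness room, branding) until Week 4. Prize-draw details cannot be given by ward beforehand. Recruitment rate then measures willingness to join under either allocation, so acceptance of the programme itself must be read from uptake, completion, drop-out and feedback after the announcement. Follow-up self-reports would still be given with the arm known, and the one-ward-per-arm limitation would remain.
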